### Enhanced Usual Care

The control group received the usual care plus the following procedures:

Participants were screened using the PHQ-9 at baseline and at 3- and 6-month follow-ups.Those with a score of 10 or more on the PHQ-9 were advised to seek appropriate mental health care.Those presenting with suicide risk were referred to specialized mental health services, by either a health professional (in Sao Paulo and Lima) or the research team (in Lima). In Lima, relatives or health care professionals were also informed depending on risk severity.All participants received at least one call after screening at inclusion, and at 3- and 6-month follow-up from the research team to assess if they had sought specialized mental health care. Those with higher risk or who did not seek care received additional phone calls.

### Time Horizon and Discount Rate

Time horizon analyses will use the study follow-up period: 3 and 6 months after the inclusion of participants in the study in order to understand its permanence effect. We truncated time horizons to the length of follow-up in the RCTs because the long-term health outcomes remain unclear and are not expected to last beyond 6 months.

Following the recommendations of the Methodological Guidelines for Economic Evaluation Studies of Health Technologies [16], we will not apply the standard discount rate of 5% on costs and benefits, because of the short (<1 year) time horizons.

### Choice of Health Outcomes and Measurement of Effectiveness

Table 1 summarizes the health outcome measures and time of collection for the outcomes that will be used in the economic evaluations.

Two health outcomes will be measured: reduction in symptoms of depression and health-related quality of life. First, the primary outcome of effectiveness for the cost-effectiveness analysis will be the proportion of patients with at least 50% reduction in PHQ-9 scores. This indicator has been used in many depression trials and is considered a robust way of symptom improvement [22].

Second, the EuroQol 5-dimensional questionnaire, 3-level version (EQ-5D-3L) will be used to measure health-related quality of life and provide utilities for estimation of quality-adjusted life years (QALYs). The EQ-5D-3L is a generic preference-based measure used in many clinical trials for a wide range of health conditions and treatments [23].

The measurement of clinical effectiveness will take place over 3 periods: baseline, 3-month follow-up, and 6-month follow-up. Both countries used the same measures (PHQ-9 and EQ-5D-3L).

**Table 1 table1:** Summary of health outcomes measured.

Health outcomes	Measures	Timing of collection	Source of data
Depressive symptoms	PHQ-9^a^	Baseline, 3-month follow-up, and 6-month follow-up	Trials’ patient-reported outcomes
Quality of life	EQ-5D-3L^b^	Baseline, 3-month follow-up, and 6-month follow-up	Trials’ patient-reported outcomes

^a^PHQ-9: 9-item Patient Health Questionnaire.

^b^EQ-5D-3L: EuroQol 5-dimensional questionnaire, 3-level version.

### Estimating Resources and Costs

The cost estimation will involve 3 stages: (1) identification of the costing items used to provide a particular service, (2) measurement of the resources used, (3) application of monetary value for each cost item, and calculation of the unit cost of a particular service [24].

The measurement of the resources will take place over 3 periods, baseline, 3-month follow-up, and 6-month follow-up, in the intervention and control groups. These are the same periods used to assess clinical effectiveness in the RCTs.

The measurement of resource use will be based on the group of patients from each country. The costing approach will apply unit cost estimates from Brazil and Peru to account for resource use in each of those countries.

Costs will be applied to the resources based on the unit costs or price weights most recently published in the respective official government databases (Department of Informatics of the National Health System, Departamento de Informática do Sistema Único de Saúde [DATASUS] in Brazil; and the Integral Health Insurance/Seguro Integral de Salud [SIS] in Peru). Other resource use not recorded in DATASUS or SIS will be based on LATIN-MH databases. These costs will be obtained in Brazilian reals (R$) and Peruvian sols (S$), as per rates in 2017. All costs will be adjusted for inflation using the Brazilian and Peruvian consumer price indexes for the current reference year (2021) and will be converted into international dollars (INT$) using the 2021 purchasing power parity (PPP) conversion factors for Brazil and Peru.

We will use a mixed costing methodology (ie, a combination of top–down and bottom–up approaches) considering 4 cost categories: intervention (CONEMO related) costs, health care costs, patient and family costs, and productivity costs. Table 2 presents an overview of resource use and cost measures that will be used in the economic evaluations. These include costs hypothesized to differ between CONEMO plus enhanced usual care (the intervention group) and enhanced usual care (the control group).

**Table 2 table2:** Summary of cost categories measured.

Cost category and unit					Unit cost		Source of data	
**Intervention (CONEMO^a^) costs**								
	Staff involved in supervision		Hour of supervision	Cost/hour		LATIN-MH^a^ databases		
	Staff involved in training		Hour of a research assistant	Cost/hour		LATIN-MH databases		
	Transport		Number of trips	Cost/trip		LATIN-MH databases		
	Dashboard and app maintenance		Maintenance charge	Cost/month		LATIN-MH databases		
	Internet package		Monthly package	Cost/month		LATIN-MH databases		
	Office supplies			Cost/month		LATIN-MH databases		
	Infrastructure			Cost/month		LATIN-MH databases		

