**Methods:**

The economic evaluation uses a within-trial analysis to evaluate the incremental costs and health outcomes of CONEMO plus enhanced usual care in comparison with enhanced usual care from public health care system and societal perspectives. Participants are patients of the public health care services for hypertension, diabetes, or both conditions in São Paulo, Brazil (n=880) and Lima, Peru (n=432). Clinical effectiveness will be measured by reduction in depressive symptoms and gains in health-related quality of life. We will conduct cost-effectiveness and cost-utility analyses, providing estimates of the cost per at least 50% reduction in 9-item Patient Health Questionnaire scores, and cost per quality-adjusted life year gained. The measurement of clinical effectiveness and resource use will take place over baseline, 3-month follow-up, and 6-month follow-up in the intervention and control groups. We will use a mixed costing methodology (ie, a combination of top–down and bottom–up approaches) considering 4 cost categories: intervention (CONEMO related) costs, health care costs, patient and family costs, and productivity costs. We will collect unit costs from the RCTs and national administrative databases. The multinational economic evaluations will be fully split analyses with a multicountry costing approach. We will calculate incremental cost-effectiveness ratios and present 95% CIs from nonparametric bootstrapping (1000 replicates). We will perform deterministic and probabilistic sensitivity analyses. Finally, we will present cost-effectiveness acceptability curves to compare a range of possible cost-effectiveness thresholds.

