## Methods

### Study Design

The economic evaluation will follow the Methodological Guidelines for Economic Evaluation Studies of Health Technologies [16] and will be reported according to the Consolidated Health Economic Evaluation Reporting Standards (CHEERS) checklist [17]. The multinational economic evaluations will be fully split analyses (incorporating estimates of both resource use and clinical effectiveness from the same group of patients from individual countries) with a multicountry costing approach (applying unit cost estimates from individual countries to account for resource use in each of those countries) [18]. The within-trial analyses will be conducted using data from the randomized control trials NCT02846662 and NCT03026426, and secondary data on health service costs extracted from governmental public databases. This protocol outlines the methods for a cost-effectiveness analysis and cost-utility analysis alongside the RCTs conducted in Brazil and Peru, respectively.

The proposed economic evaluations will be conducted from both the public health care system perspective (including only health care system costs) and the societal perspective (including health care system costs plus patient and productivity costs).

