**Health care costs**								
	Psychiatrist visits		Number of visits	Cost/visit		CEI^b^ and ISSM^c^		
	Family physician visits		Number of visits	Cost/visit		CEI and ISSM		
	Psychologist visits		Number of visits	Cost/visit		CEI and ISSM		
	Emergency room visits		Number of visits	Cost/visit		CEI, ISSM, and SAEs^d^		
	Hospital admissions		Number of hospital admissions	Cost/hospital admission		CEI, ISSM, and SAEs		
	Medicines		Number of doses	Cost/dose		CEI and ISSM		

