## Results

Phase 1 of the project ran from September 2016 to April 2018 to assess the applicability of CONEMO. Phase 2 began in June 2018 and is expected to be completed in September 2021. The economic evaluation of CONEMO will be conducted during this phase. Results will be used to report the costs of CONEMO to help plan the implementation of the intervention. The evaluation will also calculate the cost-effectiveness of CONEMO to improve symptoms of depression.

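### Table 2 counts CONEMO training in research-assistant hours from project records, and no rule prices training or supervision at public-sector pay for the public-system ICER

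*Protocol article*

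**What the plan says.** Table 2 (Methods, Estimating Resources and Costs) has seven rows under intervention costs: supervision staff, training staff, transport, dashboard and app maintenance, internet package, office supplies and infrastructure. Each names "LATIN-MH databases" as its source. The training row is counted by "Hour of a research assistant" and the supervision row by the hour of supervision; both carry a cost per hour.

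The text before the table sets an order of price sources. The main rule is "Costs will be applied to the resources based on the unit costs or price weights most recently published in the respective official government databases", meaning DATASUS and SIS. The fallback is "Other resource use not recorded in DATASUS or SIS will be based on LATIN-MH databases". The abstract states: "We will collect unit costs from the RCTs and national administrative databases".

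Study Design defines the "public health care system perspective (including only health care system costs". The Intervention Costs section treats CONEMO as already operational. It leaves out start-up costs and the research costs of running the trials, but keeps staff time for training and supervising primary care workers. On the use of the figures, the Results section says: "Results will be used to report the costs of CONEMO to help plan the implementation of the intervention".

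**The concern.** A public-system analysis asks what the health system would pay to run the service. The trial is a sound source for how many hours training and supervision took. It is a weaker source for the price of an hour if that price is a research project's pay rate, because the health system pays its own staff on its own scales. The training row goes further and names a research post as the unit, and nothing in the article converts that post to a health-system grade or wage.

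Two results depend on the price. One is the public-system ICER, where CONEMO staff cost sits in the numerator. The other is the cost of CONEMO itself, which is to be reported for implementation planning and would be read as what the public system should budget.

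**Working it through.** The article gives no unit cost, wage, number of hours or ICER, so there is no figure of the plan to reproduce. The check is a reading of the costing text, then algebra, then an illustration on assumed values.

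**1. Does LATIN-MH supply prices or only quantities?** The source column of Table 2 does not settle it, because it is used in two ways:

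- Health care rows name trial instruments and adverse-event reports, for example "CEI, ISSM, and SAEs" for emergency visits and admissions. These appear to supply counts; the prices come from the DATASUS/SIS rule.
- Patient and productivity rows name price sources: average public transport cost, market price, average hourly wage.
- Intervention rows name LATIN-MH, which could be either.

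Three places outside that column point to prices. The abstract says that unit costs, not only quantities, come from the trials. The sentence after the LATIN-MH fallback says that the costs will be obtained in local currency, so the fallback yields money values. No other price source is given for any intervention row. Project rates are therefore the natural reading, although the article does not say so outright.

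**2. Where does a price gap go?** I take intervention cost to be part of the public-system perspective. Write

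- I = mean intervention cost per CONEMO patient,
- H1, H0 = mean health care cost per patient in the CONEMO and control arms, both at DATASUS/SIS prices.

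Then incremental cost = I + H1 − H0. Let h be the training and supervision hours per CONEMO patient, and let p(project) and p(public) be the two hourly prices. Changing the price changes I only:

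shift in incremental cost = h × [p(project) − p(public)]

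shift in ICER = that amount ÷ mean difference in effect

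Nothing in H1 − H0 offsets it.

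**3. Illustration, on assumed values only.** Let s be the share of I, as planned, that is training and supervision staff, and let r = p(project) ÷ p(public). The error as a share of the planned I is s × (1 − 1/r). Neither s nor r is in the document. I take s from 0.3 to 0.7, and r from 0.8 (that is, 1/1.25) to 2.

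| r | 1 − 1/r | s = 0.3 | s = 0.7 |
|---|---|---|---|
| 0.8 | −0.25 | −7.5% | −17.5% |
| 1.0 | 0 | 0% | 0% |
| 1.25 | 0.20 | 6% | 14% |
| 2.0 | 0.50 | 15% | 35% |

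A positive entry means that CONEMO is costed too high, a negative one too low. The table shows how the error behaves; it does not estimate it.

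**The case against.** The case against is substantial, and parts of it limit the point.

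- **All seven rows are wrong.** A reader might infer this from the uniform source column. The document does not support it. Only the training row names a research post. The supervision row names no grade, and the description of the intervention says that psychologists supervised. For app maintenance, internet and the like, project records are an ordinary bottom-up source, and the fallback is openly stated.
- **Only comparator care gets government prices.** This is also tempting and also wrong. DATASUS/SIS prices apply to health care use in both arms; the contrast is between the intervention and health care categories.
- **LATIN-MH may supply hours only.** This is possible, since the source column is mixed. If so, the article gives no price source for these hours, and Table 2 still needs the entry.
- **The sensitivity analysis covers it.** Unit costs will be varied one at a time, and the limitations admit that some items are proxies. Both help, but general variation does not correct the base case and does not tie the range to a public wage.
- **The article is condensed.** Grades and on-costs are details often left to a fuller plan. The point does not rest on their absence, however: the research-assistant hour is a choice printed in Table 2.

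**Conclusion.** The point holds as an improvement to the costing rule for two rows, training and supervision. It is clearest for training, where the stated unit is a research post. It rests on the natural reading that LATIN-MH supplies the hourly price, and on intervention cost being counted in the public-system perspective.

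Its size and direction are unknown. A reader might infer that CONEMO is overcosted, or that the gap could carry the ICER across a threshold. The document supports neither: it contains no pay ratio, staff share or CONEMO cost per patient, and if project pay is below public pay the error reverses. What is certain is the mechanism. Any gap falls in one arm and reaches the incremental cost undiluted.

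**What to change.** In Table 2 and the Intervention Costs section:

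1. Keep LATIN-MH databases as the source of training and supervision **hours**.
2. For the public-system base case, price those hours at public-sector pay, with on-costs, of a stated staff category in each country: the staff who would train and supervise in routine service. Replace the research-assistant unit accordingly and name the pay scale. In Lima the sites belong to two providers, EsSalud and MINSA, so say whose scale is used.
3. Put the pay rates on the same footing as the other costs, which are taken at 2017 rates, inflated to 2021 and converted by PPP.
4. Report the ICER at LATIN-MH project rates as a named sensitivity analysis.
5. Leave transport, app maintenance, internet, office supplies and infrastructure on LATIN-MH records.

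The cost is a pay-scale look-up in two countries and a short edit, with no new data collection. The downside is that an observed project rate gives way to an assumed staff category, which has to be stated; the sensitivity analysis shows how much that assumption matters.

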**Health care costs**								
	Psychiatrist visits		Number of visits	Cost/visit		CEI^b^ and ISSM^c^		
	Family physician visits		Number of visits	Cost/visit		CEI and ISSM		
	Psychologist visits		Number of visits	Cost/visit		CEI and ISSM		
	Emergency room visits		Number of visits	Cost/visit		CEI, ISSM, and SAEs^d^		
	Hospital admissions		Number of hospital admissions	Cost/hospital admission		CEI, ISSM, and SAEs		
	Medicines		Number of doses	Cost/dose		CEI and ISSM		
**Patient and family costs**								
		Transport	Number of trips	Cost/trip		Average cost for public transport		
		Internet	Monthly package	Cost/month		Average market price		
**Productivity costs**								
		Days of work lost	Number of days	Cost/hour		Average hourly wage		

^a^CONEMO: control emotional (emotional control intervention).

^b^LATIN-MH: Latin America Treatment and Innovation Network in Mental Health.

^c^CEI: Cost-Effectiveness Instrument.

^d^Mental Health Instrument.

^e^SAE: Serious Adverse Events Report.

### Intervention Costs

Intervention costs include the value of the staff time and transport involved in either supervision or training of the primary care workers that will use CONEMO.

We will assume that the intervention (CONEMO) is operational, and so start-up costs, such as design and development of CONEMO, will be excluded. Therefore, we will include only costs for maintenance of the dashboard and app, internet package costs, and expenditures related to office supplies and infrastructure.

All of the research-related costs associated with trial administration, data collection, and outcome assessment of RCTs will be excluded.

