### CONEMO Plus Enhanced Usual Care

The intervention group received CONEMO plus enhanced usual care. CONEMO is a low-intensity mHealth intervention aimed at reducing symptoms of depression. It is delivered via a smartphone app, and is minimally supported by a nurse/NA. The CONEMO app delivers 18 brief, automated mini-sessions over a 6-week period, with 3 mini-sessions per week. Each session is completed in less than 10 minutes.

The app content is based on behavioral activation, an evidence-based psychological approach to treat depression. Processed data on app usage were collected automatically and reviewed in real-time by nurses/NAs through a dashboard installed on tablets.

Nurses/NAs met with participants for an initial face-to-face meeting, where participants received a smartphone with the app preinstalled and completed a tutorial on its use. Nurses/NAs made 2 mandatory phone calls to all CONEMO participants at the beginning of the program to troubleshoot any difficulties and enhance motivation for the use of CONEMO. Additional calls were prompted through notifications sent to nurses/NAs when the CONEMO automated system detected nonadherence. Patients could request technical help through the help button on the app. Nurses/NAs received training and were supervised weekly by psychologists through face-to-face meetings or via telephone.

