## Discussion

### Overview

Assessing the economic viability of the CONEMO intervention based on its cost-effectiveness will enable us to ascertain the feasibility of its implementation in primary and secondary care. If shown to be financially viable, the intervention could help bridge the treatment gap and increase access to mental health care. If the ICER is favorable, there would be a strong case for policymakers to support the scale-up of this intervention.

Implementing the CONEMO intervention would enable the screening, identification, and treatment of depression in patients with chronic diseases. The expected result is a reduction in symptoms and likely an increase in self-care, adherence to treatment, and quality of life. These outcomes could also result in fewer complications and required resources, as well as reduced health care costs. Using nursing staff to support patients rather than specialized mental health professionals and specialized services could also be an efficient use of human resources, thereby saving costs in the longer term.

Economic evaluations are particularly important because they can be used to guide decision makers or funders in determining if the mHealth interventions improve health outcomes when compared to other existing interventions [15]. They are also important for analyzing whether the cost to adopt and maintain the intervention in a health system is justified. One of the barriers of mHealth implementation and scale-up is the financial feasibility, yet few studies include or detail operational costs of mobile communication, such as fees charged to end users (patients).

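### Supervision and training are the only staff time priced under intervention costs, so the nurse/NA time that delivers CONEMO is valued at zero and the incremental cost is biased downward

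*Protocol article*

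**What the plan says.** The section on CONEMO plus enhanced usual care describes the nurse/NA work that supports the app:

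- "Nurses/NAs met with participants for an initial face-to-face meeting", at which the participant received the phone and completed a tutorial.
- "Nurses/NAs made 2 mandatory phone calls to all CONEMO participants at the beginning of the program".
- Further calls followed when the system flagged nonadherence.
- App-use data were "reviewed in real-time by nurses/NAs through a dashboard installed on tablets".

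On pricing, the Intervention Costs section states: "Intervention costs include the value of the staff time and transport involved in either supervision or training of the primary care workers". After excluding design and development as start-up costs, it continues: "Therefore, we will include only costs for maintenance of the dashboard and app, internet package costs, and expenditures related to office supplies and infrastructure". The intervention block of Table 2 has two staff rows, "Staff involved in supervision" and "Staff involved in training"; the unit of the second is an hour of a research assistant. The other rows are transport, dashboard and app maintenance, internet, office supplies and infrastructure.

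The text introducing Table 2 (Estimating Resources and Costs) says that its items include costs hypothesized to differ between the two arms.

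**The concern.** Delivery labour differs between the arms by design. The nurse/NA tasks are described only for CONEMO, and the follow-up calls in enhanced usual care are made by the research team. If this time has no cost line, the CONEMO arm is costed without the people who deliver it. The difference in mean cost is the numerator of both planned ratios: cost per patient with at least a 50% PHQ-9 reduction, and cost per QALY. Health care system costs enter both the public health care and the societal perspective, so neither escapes.

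The protocol also says that the results will be used to report the costs of CONEMO for planning its implementation. A planner would receive a figure that omits delivery staff. The Discussion suggests that "Using nursing staff to support patients rather than specialized mental health professionals and specialized services could also be an efficient use of human resources"; an analysis that prices that nursing time at zero could not inform this.

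**Working it through.** The plan states no nurse hours, wage, unit cost or expected incremental cost, so there is no figure to reproduce. The main check sets delivery tasks against cost lines. The arithmetic after it only illustrates scale.

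**Step 1. Is there a line for each task?**

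| Nurse/NA task (CONEMO arm) | Intervention costs | Health care costs | Patient and productivity costs |
|---|---|---|---|
| Initial meeting and tutorial | none | none | none |
| Two mandatory calls | none | none | none |
| Calls on nonadherence | none | none | none |
| Dashboard review | system maintenance only, not staff time | none | none |

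The health care rows are psychiatrist, family physician, psychologist and emergency room visits, admissions and medicines. None is a nurse/NA contact. The patient and family rows are transport and internet, and the productivity row is the patient's lost work. The two stated exclusions do not explain the gap: delivery time is neither a start-up cost nor trial administration, data collection or outcome assessment.

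**Step 2. Direction.** Incremental cost = mean cost (CONEMO arm) − mean cost (control arm). Leaving out a positive cost that arises only in the CONEMO arm lowers this difference. With a positive incremental effect, each ratio is then too low.

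**Step 3. Illustrative cost per participant.** All durations and wages here are assumptions.

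- Low: 30 min meeting + 2 × 5 min calls + no prompted calls + 6 weeks × 2 min dashboard = 52 min. At INT$5 per hour: 52/60 × 5 = INT$4.33.
- High: 60 min + 2 × 20 min + 4 × 15 min + 6 × 10 min = 220 min. At INT$20 per hour: 220/60 × 20 = INT$73.33.

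**Step 4. Compare with what the thresholds allow.** Largest acceptable incremental cost = threshold × QALY gain. The thresholds are those in Sensitivity Analyses; the gain of 0.01 QALY is assumed.

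| | Lower threshold | Upper threshold |
|---|---|---|
| Brazil | 3210 × 0.01 = INT$32.10 | 10,122 × 0.01 = INT$101.22 |
| Peru | 1969 × 0.01 = INT$19.69 | 7747 × 0.01 = INT$77.47 |

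Share taken by the omitted item:

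- Brazil: 4.33/101.22 = 4% to 73.33/32.10 = 228%.
- Peru: 4.33/77.47 = 6% to 73.33/19.69 = 372%.

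The upper ends pair the highest assumed cost with the lowest threshold, so they are extremes and not expectations.

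**Step 5. Shift in the ratios** = omitted cost / incremental effect.

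- Per QALY: INT$867-14,667 at a gain of 0.005, INT$433-7,333 at 0.01, and INT$217-3,667 at 0.02.
- Per responder, for assumed differences in response of 5, 10 and 20 percentage points: INT$87-1,467, INT$43-733 and INT$22-367.

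**The case against.** The best defence is that the list is not truly closed. The first sentence of Intervention Costs says that the costs include certain items. The word "only" appears in the next paragraph, as a consequence of dropping start-up costs. Read literally, that second sentence would also exclude the supervision and training just named, so it cannot be the full list. Table 2 is called an overview, and the article condenses a longer protocol. This has some force: one cannot say that the time will never be costed in practice. It does not rescue the rule as written. Both places that define staff costs name the same two activities, and the stated criterion for inclusion calls for delivery time.

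The protocol might instead regard nurses as existing salaried staff with no extra cost. It states no such assumption, and it prices physician and psychologist visits. The planned one-way analyses vary key parameters of the analysis; they do not supply an item that has no line.

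A reader might infer more than the documents support:

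- That nothing but supervision and training is priced. Maintenance, internet, office supplies and infrastructure are priced too; the gap concerns staff time.
- That nurses' attendance at training and supervision is left out. The wording does not limit those hours to the supervisor's, although the training row does name a research assistant.
- That the tablets are unpriced. Infrastructure is undefined and could hold them.
- That answering help requests is unpriced nurse work. The protocol does not say who answered them.

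**Conclusion.** The concern holds for nurse/NA time in the initial meeting, the mandatory and prompted calls, and dashboard review. As written, that labour is valued at zero, contrary to the plan's own criterion, and the incremental cost is biased in favour of CONEMO under both perspectives and in both countries. The direction needs no assumption beyond this time having a positive cost.

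The size cannot be determined from the documents. Under the assumed INT$4-73 per participant and a 0.01 QALY gain, it could be negligible or could exceed the whole incremental cost that the thresholds allow. A reader might conclude that the omission would by itself reverse the finding on cost-effectiveness. That is not shown: it depends on the actual hours, wages, QALY gain and all other incremental costs and savings, none of which the documents give. The Discussion's remark on nursing staff is likewise conditional and linked to longer-term savings, beyond the 6-month horizon, so it is not a hypothesis that this analysis sets out to test.

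**What to change.** Add a nurse/NA delivery-time item to Intervention Costs and to Table 2, covering the initial meeting with tutorial, mandatory and prompted calls, and dashboard review, each valued at the local nurse/NA hourly cost in Brazil and Peru. Use contact or notification counts from the trials where they exist. Where minutes were not recorded, state a minutes-per-contact assumption and vary it in the one-way sensitivity analysis. If the authors do intend zero opportunity cost, they should say so and justify it.

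In the same edit, state whether supervision and training hours include the attending nurses/NAs, and whether infrastructure includes the tablets.

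The cost is some extra costing work, reliance on assumed durations where none were logged, and a less favourable ratio for CONEMO. No new trial procedure is needed.
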